### Outcome measure

2.7

The outcome is the identified potential differences deep learning features between GC without PM group and GC with PM group will be the outcome measures.

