**Method::**

All patients with gastric cancer were retrospectively enrolled. All patients were initially diagnosed as PM negative by CT and later confirmed as positive through surgery or laparoscopy. The dataset was randomly split into training cohort (70% of all patients) and testing cohort (30% of all patients). To develop deep convolutional neural network (DCNN) models with high generalizability, 5-fold cross-validation and model ensemble were utilized. The area under the receiver operating characteristic curve, sensitivity and specificity were used to evaluate DCNN models on the testing cohort.

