### Study aims

2.1

The aim of this study is to develop a deep learning model for accurate preoperative diagnosis of PM in GC.

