#### Development of the deep learning-based model

2.6.3

In brief, we adopted a deep convolutional neural network with Depthwise Convolution blocks and Fully Connection layer constructing a classifier. This classifier was designed to determine the probability of a patient having an occult PM. For training the model can predict occult PM, we used weighted cross-entropy loss to supervise the model's parameter optimization direction.

Finally, for each input of CT image, the deep learning-based model provided a continuous value between 0 and 1 as the probability of occult PM, and the process is shown in Figure 2.

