### Statistical analysis

2.10

The differences of continuous variables were analyzed by the Mann–Whitney *U* test, and the differences of categorical variables were analyzed by the Chi-square test. The accuracy of the deep learning-based model was assessed with the receiver operating characteristic (ROC) curve and area under the ROC curve. Delong test was used to compare the ROC curves of models. The calibration of the model was assessed using the calibration curves. In addition, sensitivity and specificity for classification were evaluated.

For the deep learning-based model, 2 different probability values were selected as classification thresholds based on the results of the in-house validation cohort: a high sensitivity threshold (75% sensitivity on in-house validation) and a high specificity threshold (75% specificity on in-house validation). Considering the group imbalance in the in-house validation cohort, we used bootstrap (resampled the in-house validation cohort 1000 times) and calculated the 95% confidence interval. Finally, the decision curve was conducted to evaluate our approach usefulness by quantifying the net benefits at different thresholds probabilities.

All these statistical analyses were performed with SPSS 22.0. A 2-tailed *P*-value less than .05 was considered statistically significant.

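### The declared outcome is a between-group difference in network features, which does not match the diagnostic-accuracy aim or the planned evaluation by AUC, sensitivity and specificity

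*Protocol article*

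**What the plan says.** Section 2.7 is the only section headed as the outcome measure, and it names one outcome: "The outcome is the identified potential differences deep learning features between GC without PM group and GC with PM group". It gives no accuracy metric, test, cohort or model.

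The rest of the article is about diagnostic accuracy:

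- Section 2.1 sets the aim, to "develop a deep learning model for accurate preoperative diagnosis of PM in GC".
- The abstract, under Method: "The area under the receiver operating characteristic curve, sensitivity and specificity were used to evaluate DCNN models on the testing cohort".
- Section 2.6.2 splits both the occult-PM and the PM-negative patients 70/30 and keeps the 30% for judging predictive performance.
- Section 2.6.3 describes a single output per image: "the deep learning-based model provided a continuous value between 0 and 1 as the probability of occult PM".
- Section 2.6.4 produces five single models, an average of all five, and a further ensemble assembled from selected single models.
- Section 2.10: "The accuracy of the deep learning-based model was assessed with the receiver operating characteristic (ROC) curve and area under the ROC curve". It adds DeLong comparisons, calibration curves, sensitivity and specificity, two cut-offs and a decision curve.

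The abstract also describes the cohort in a way the body does not: "All patients were initially diagnosed as PM negative by CT and later confirmed as positive through surgery or laparoscopy".

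**The concern.** The declared outcome should be the quantity that answers the aim. Here the aim asks how well a model separates CT-negative patients with and without PM, while the outcome asks whether some network feature differs between those groups. The second can be true when the answer to the first is disappointing.

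Two consequences follow. First, a report could say that the declared outcome was met on the strength of a feature difference, with discrimination too weak to guide who goes to laparoscopy. Second, no accuracy result is marked as the one that carries the conclusion. Several models and several accuracy measures are planned, so the headline could be settled after the results are seen.

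The abstract sentence is a separate and smaller matter. Read literally it leaves no PM-negative patients, and specificity and AUC cannot be defined without them.

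**Working it through.** The point is textual and depends on no calculated figure. The only design number is the sample size of at least 109 (2.9). It cannot be reproduced, because the article gives no target AUC, power, prevalence or precision. It therefore cannot show whether the study was sized for 2.7 or for an accuracy target.

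**1. The sections side by side**

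| Place | Quantity named |
|---|---|
| 2.1 Aim | Accuracy of preoperative diagnosis |
| Abstract, Method | AUC, sensitivity, specificity in the testing cohort |
| 2.6.3 | One probability per image |
| 2.10 | ROC/AUC, calibration, sensitivity, specificity, net benefit |
| 2.7 Outcome | Group differences in network features |

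Only 2.7 refers to features as something to be compared. The article does not say what a feature is, how it is extracted, in which cohort it is compared or by which test. The Mann-Whitney sentence in 2.10 concerns continuous variables in general and does not mention features.

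**2. How little a significant difference can mean (illustration)**

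Suppose one feature were compared by a Mann-Whitney test at two-sided .05. By the Noether approximation, with N patients and PM share c, significance is reached at an observed

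AUC = 0.5 + 1.96 / √(12 · c · (1 − c) · N).

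The PM share among eligible patients is not given, so c is an assumption. The article's 16% is the share of PM that goes undetected and appears here only as one value in the range.

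| c (assumed) | 12·c·(1−c)·109 | AUC at P=.05, N=109 | AUC at P=.05, N=32.7 |
|---|---|---|---|
| 0.10 | 117.7 | 0.68 | 0.83 |
| 0.16 | 175.8 | 0.65 | 0.77 |
| 0.30 | 274.7 | 0.62 | 0.72 |
| 0.50 | 327.0 | 0.61 | 0.70 |

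The last column uses 0.30 × 109 = 32.7, the size of the held-out part if exactly 109 patients were enrolled. There the observed AUC must be higher, but only because the sample is small: a result at this boundary is only just distinguishable from 0.5. In either column, significance shows that the AUC is not 0.5. It does not show that the model is accurate.

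**3. How many results could carry the conclusion**

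Section 2.6.4 gives 5 + 1 + 1 = 7 models (fewer distinct ones if the selected ensemble keeps all five). Each has an AUC, so there are up to 7. The two cut-offs add specificity at 75% sensitivity and sensitivity at 75% specificity. If these apply to the final model only, there are 7 + 2 = 9 candidate figures. If they apply to every model, there are 7 × 3 = 21. Section 2.7 selects none of them.

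**4. The abstract sentence**

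Specificity is true negatives divided by all PM-negatives, so with no PM-negatives the denominator is zero. But 2.6.2 splits both groups, 2.7 compares both, the CT criterion in 2.4.1 does not require confirmed PM, and the abstract itself lists specificity and AUC. The body settles the matter: the sentence is misworded.

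**The case against.** The strongest reply is that accuracy is already pre-planned. The abstract and 2.10 name the metrics, 2.6.2 reserves the evaluation cohort, and 2.10 names both operating points. On this view only a label is missing from 2.7, and a hierarchy of outcomes may stand in a fuller protocol or analysis plan. The first part stands: accuracy analysis is not absent, and correcting 2.7 would leave the planned analyses, cohort and reference standard as they are. The second part does not remove the point, because 2.7 is not silent. It states an outcome, and that outcome is not the one the aim needs.

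A second reply is that 2.7 may loosely mean the model's probability, the only output described. A Mann-Whitney comparison of that score is a rank test of AUC = 0.5, since U/(n₁n₂) equals the AUC. On that reading 2.7 does bear on discrimination. It would still test only whether there is any discrimination, and the text would still need to say so.

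A reader might infer that the outcome cannot fail, because the network is trained to separate the two groups. The documents do not support this. Training pushes the groups apart in the training data, but features of an overfitted network need not differ in held-out patients, and 2.7 does not say which cohort is meant. A reader might also want to count chance findings over a large set of features. The article gives no number of features, does not assign a test to them, and gives no ground for treating features of one network as independent, so no such figure is offered here.

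Setting the cut-offs on the validation cohort (2.10) and the loose selection rule for the ensemble (2.6.4) are separate matters, which rewording 2.7 would not resolve.

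**Conclusion.** The point holds as a mismatch between the declared outcome and both the aim and the planned evaluation. That rests on the text alone. The illustration of size (P<.05 at an AUC of about 0.61 to 0.68 with 109 patients) assumes one feature, a Mann-Whitney test, comparison in all 109 patients and a PM share of 10% to 50%. The conclusion does not depend on it. The count of 9 to 21 candidate figures depends on whether the cut-offs apply to one model or to all.

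This should be corrected before results are reported, but it does not invalidate the design. The abstract sentence is a clerical slip. A reader might infer from it that specificity and AUC could never be computed, but the body plainly includes a PM-negative group and no planned analysis would change.

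**What to change.** Replace the text of 2.7 with wording such as:

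> Primary outcome: the AUC, with 95% confidence interval, of the final ensemble model in the in-house validation cohort, with PM status at surgery or laparoscopy as reference standard. The final ensemble is specified before the validation cohort is analysed. Secondary outcomes: sensitivity and specificity of that model in the same cohort. Differences in network features between groups are exploratory.

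State in 2.6.4 which ensemble is the final one, and that the single models and the other ensemble are supporting analyses. State in 2.10 that the bootstrap interval already planned there applies to this AUC. If feature differences are kept, define the feature, the cohort and the test.

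In the abstract, say that patients negative on CT were later confirmed as PM positive or PM negative at surgery or laparoscopy, in line with 2.6.2.

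The cost is a few sentences, with no new data and no new analysis. The registry record was not available. If it carries the wording of 2.7, it should be aligned.

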### Data collection and management

2.8

Data will be processed anonymously, omitting the information that can identify the participant's individual identity. Strict safety and confidentiality measures will be established in the archives of clinical trial institutions.

### Sample size calculation

2.9

We calculated the number of patients needed considering the epidemiology of PM in GC; the estimated sample size was at least 109.

### Statistical analysis

2.10

The differences of continuous variables were analyzed by the Mann–Whitney *U* test, and the differences of categorical variables were analyzed by the Chi-square test. The accuracy of the deep learning-based model was assessed with the receiver operating characteristic (ROC) curve and area under the ROC curve. Delong test was used to compare the ROC curves of models. The calibration of the model was assessed using the calibration curves. In addition, sensitivity and specificity for classification were evaluated.

For the deep learning-based model, 2 different probability values were selected as classification thresholds based on the results of the in-house validation cohort: a high sensitivity threshold (75% sensitivity on in-house validation) and a high specificity threshold (75% specificity on in-house validation). Considering the group imbalance in the in-house validation cohort, we used bootstrap (resampled the in-house validation cohort 1000 times) and calculated the 95% confidence interval. Finally, the decision curve was conducted to evaluate our approach usefulness by quantifying the net benefits at different thresholds probabilities.

All these statistical analyses were performed with SPSS 22.0. A 2-tailed *P*-value less than .05 was considered statistically significant.

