#### Data management

2.6.2

For the development of the deep learning-based model, all patients’ CT images with PM-negative and patients’ CT images with occult PM, were randomly allocated into 1f of 2 cohorts:

(1)the training data cohort contains 70% patients of occult PM and 70% patients of PM-negative, and 5-fold cross-validation was used to optimize the network weight;(2)the in-house validation data cohort comprising 30% patients of occult PM and 30% patients of PM-negative to evaluate the predictive performance of the deep learning-based model.

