#### Evaluation of the deep learning-based model

2.6.4

We get 5 different single models via 5-fold cross-validation. Then, we carry out all 5 models as a vanilla ensemble model, averaging the predicted risk values of the 5 single models. We analyzed the ROC consistency between the Vanilla ensemble model and each single model. Moreover, we selected each single model as the candidate model based on the above analysis results, and then assembled these to obtain our ensemble model. We evaluate the performance of models on the in-house validation cohort.

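### Both cut-offs are set to reach 75% on the in-house validation cohort, so those two figures are inputs, and no pre-locked cut-off is tested on unseen patients

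*Protocol article*

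**What the plan says.** Section 2.10 (Statistical analysis) fixes the source of the cut-offs: "2 different probability values were selected as classification thresholds based on the results of the in-house validation cohort". The first is "a high sensitivity threshold (75% sensitivity on in-house validation"; the second is "a high specificity threshold (75% specificity on in-house validation". The same paragraph obtains 95% confidence intervals from 1000 bootstrap resamples of that cohort.

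Elsewhere the article gives this cohort a different job. Section 2.6.2 (Data management) sets aside "30% patients of occult PM and 30% patients of PM-negative to evaluate the predictive performance of the deep learning-based model". Section 2.6.4 says "We evaluate the performance of models on the in-house validation cohort". The abstract describes a two-way division, "The dataset was randomly split into training cohort (70% of all patients) and testing cohort (30% of all patients", and names AUC, sensitivity and specificity as the measures: "sensitivity and specificity were used to evaluate DCNN models on the testing cohort". The study is single-center (section 2.2), and no third or external cohort is described.

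**The concern.** A held-out cohort is useful because nothing about the classification rule has been tuned on it. Here the rule is completed on it. If the cut-off is whichever value gives 75% sensitivity in these patients, then 75% sensitivity in these patients is not a finding about the model. The same holds for 75% specificity at the second cut-off.

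The Discussion presents the model as a help in choosing patients for laparoscopy. A use of that kind depends on a cut-off. Under the plan as written, the accuracy of a fixed cut-off in patients who did not help to choose it is never estimated, and the limitations paragraph does not mention this.

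**Working it through.** **Inputs from the article.** Target 75% for each cut-off, reached on the in-house validation cohort (2.10). Validation share 30% of each class (2.6.2). Total sample size at least 109 (2.9), so at the minimum about 0.30 × 109 = 32.7, or 33 validation patients.

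**Assumptions.** The article does not give the proportion of eligible patients with occult PM, so the number n of occult-PM cases in the validation cohort is shown as a range. At N = 109, shares of 16%, 30% and 50% give n = 5, 10 and 16. Larger n stands for a study above its minimum size. The article also does not say which of the qualifying cut-off values is taken.

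**Step 1: is the 75% a result or an input?** Take the highest cut-off with observed sensitivity of at least 75%. It classifies k = ceil(0.75n) of the n cases as positive, so the observed sensitivity is k/n whatever the scores are:
- n = 5: 4/5 = 80%
- n = 10: 8/10 = 80%
- n = 16: 12/16 = 75%

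The AUC does not enter. A simulation (5000 replicates per setting, binormal scores, true AUC 0.50, 0.70 and 0.85) agrees: observed sensitivity at the first cut-off had standard deviation 0.000 and was identical for all three AUCs. Observed specificity at the second cut-off likewise did not change with AUC (0.750 to 0.783 at N = 109). Small cohorts can step above 75%, but the value is still fixed by the rule.

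**Step 2: what is the true sensitivity at that cut-off?** With the cut-off at the k-th highest case score, true sensitivity follows Beta(k, n+1−k), with mean k/(n+1), whatever the AUC. If the cut-off is placed elsewhere between the k-th and (k+1)-th highest case scores, the observed value stays k/n, but the mean true value can rise to (k+1)/(n+1).

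| n (assumed) | k | Observed k/n | Mean, highest qualifying cut-off, k/(n+1) | 95% range at that cut-off | Upper limit of mean, (k+1)/(n+1) |
|---|---|---|---|---|---|
| 5 | 4 | 80% | 4/6 = 67% | 28-95% | 5/6 = 83% |
| 10 | 8 | 80% | 8/11 = 73% | 44-93% | 9/11 = 82% |
| 20 | 15 | 75% | 15/21 = 71% | 51-88% | 16/21 = 76% |
| 50 | 38 | 76% | 38/51 = 75% | 62-85% | 39/51 = 76% |

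The observed value always lies between the two limits for the mean, so the direction of any bias depends on the placement rule. The spread does not vanish under either placement.

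The same argument applies to specificity at the second cut-off, with the PM-negative patients in place of the cases. With 28 negatives and the lowest qualifying cut-off, the observed value is 21/28 = 75% and the mean true value is 21/29 = 72%.

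**Step 3: what remains informative?** In the simulation at N = 109, specificity at the first cut-off was 0.27-0.34, 0.53-0.59 and 0.78-0.81 for AUC 0.50, 0.70 and 0.85, and on average it matched the value in new patients (for example 0.585 against 0.585 with 5 cases and AUC 0.70). The companion figure does separate a useless model from a good one.

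**The case against.** The strongest reply is that the damage is contained. Section 2.10 assesses accuracy first by the ROC curve and AUC, with DeLong comparisons, calibration and decision curves; none of these uses the two cut-offs. Sensitivity and specificity come in addition. The article openly defines the 75% as the threshold criterion and never calls it a validated result. Each cut-off also yields a second figure that is not fixed. All of this stands. A reader might infer that the whole validation is void or that a useless model would pass unnoticed; the documents do not support that, because AUC and the companion figures would expose it.

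A reader might also infer that true sensitivity must be lower than reported. That holds on average only for the highest qualifying cut-off. The article does not state the placement rule, and other placements allow a mean above the observed value (up to 83% against 80% with 5 cases).

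Nor can the bootstrap interval be dismissed outright. The text does not say which quantity receives it or whether cut-offs are re-derived in each resample. Only if they are held fixed does the interval omit the uncertainty from choosing them.

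Finally, no single sentence says that performance at these cut-offs is reported on the same cohort. That follows from 2.6.2, 2.6.4 and the abstract taken together, with only two cohorts described. None of these replies removes the core problem: the cohort reserved "to evaluate the predictive performance of the deep learning-based model" also completes the rule being evaluated.

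**Conclusion.** The point holds for the two 75% figures and for the lack of a test of a locked rule. Sensitivity at the first cut-off and specificity at the second are set by the plan, whatever the model's discrimination and at any sample size. Neither sensitivity-specificity pair shows how a pre-specified cut-off performs in unseen patients. It does not extend to AUC, the ROC curve or the companion figures.

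The resulting uncertainty is large if the validation cohort holds few occult-PM cases and modest if it holds many: the 95% range for true sensitivity is 28-95% with 5 cases and 62-85% with 50. These ranges rest on assumed case numbers and on the highest qualifying cut-off being used; the direction of bias is not determined by the documents.

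**What to change.** In section 2.10, select both cut-offs from the out-of-fold predictions of the 5-fold cross-validation in the training cohort and lock them. Apply them unchanged to the ensemble score in the in-house validation cohort, and report both the sensitivity and the specificity obtained there, each with a 95% CI. State how the cut-off is placed when several values qualify.

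The cost is a short edit and no additional patients; the fold models already needed for section 2.6.4 can supply the predictions. The drawback is that the achieved values may miss 75%, partly because out-of-fold scores come from single models while the final score is their average, so a cut-off may not transfer exactly. Such a miss is what the validation cohort is there to show.

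If the cut-offs must stay as they are, the minimum is to label the two 75% values as chosen operating points and not as validated performance, and to state whether the bootstrap re-derives the cut-offs in each resample.

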We hope that the deep learning-based model can be an excellent prediction ability of occult PM and may have significant clinical implications on early detection of occult PM for AGC.

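### With both targets at 75% and no ordering rule, the 'high sensitivity' and 'high specificity' cut-offs trade places whenever the ROC curve passes above 75%/75%

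*Protocol article*

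**What the plan says.** The model returns "a continuous value between 0 and 1 as the probability of occult PM" (section 2.6.3), so a higher score means that occult peritoneal metastasis (PM) is more likely. Accuracy is "assessed with the receiver operating characteristic (ROC) curve and area under the ROC curve" (section 2.10).

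The same section adds two operating points: "2 different probability values were selected as classification thresholds based on the results of the in-house validation cohort". They are defined as "a high sensitivity threshold (75% sensitivity on in-house validation) and a high specificity threshold (75% specificity on in-house validation"). Nothing says which cut-off must be the lower, or what happens if they cross.

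No expected or target AUC is given. The closing sentence of the Discussion expresses the ambition in words only: "We hope that the deep learning-based model can be an excellent prediction ability of occult PM". On size, section 2.9 says "the estimated sample size was at least 109", and section 2.6.2 puts "30% patients of occult PM and 30% patients of PM-negative" in the validation cohort.

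**The concern.** Two labelled operating points are useful when they serve opposite purposes: a low cut-off that misses few cases, and a high cut-off that raises few false alarms. Each definition here fixes only the measure it is named after and leaves the other free. With both targets at the same moderate value, a good model exceeds 75% on the free measure at each cut-off, and the names then describe the wrong cut-offs.

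The Discussion names two uses: avoiding improper management of patients with occult PM, and choosing candidates for laparoscopy. A reader who takes the cut-off labelled high sensitivity in order to miss fewer cases would, with a good model, get the one of the two that misses more. If the authors noticed this and renamed the cut-offs, they would be changing the plan after seeing the validation results.

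**Working it through.** **Plan's own figure.** There is none to reproduce. The article states no AUC or crossing point. The minimum of 109 comes without the inputs needed to check it, and the argument below does not depend on it.

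**Inputs.** Both targets are 0.75 (section 2.10). The score is continuous and rises with the probability of occult PM (section 2.6.3). The validation share is 30% (section 2.6.2) of at least 109 (section 2.9): 0.30 × 109 = 32.7, about 33. The ROC shape and the number of PM-positive patients in validation are my assumptions.

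**Step 1: general condition, no distribution assumed.** Lowering a cut-off cannot reduce sensitivity or raise specificity. Suppose sensitivity exceeds 75% at the cut-off giving 75% specificity. To bring sensitivity down to 75% the cut-off must be raised. The 75%-sensitivity cut-off is then the higher of the two, so it is the less sensitive and the more specific. The labels reverse exactly when the ROC curve passes above 75%/75%.

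**Step 2: equal-variance binormal ROC.** Let PM-negative scores be N(0,1) and PM-positive scores N(d,1), so AUC = Φ(d/√2). With z(0.75) = 0.6745:
- 'High sensitivity' cut-off: d − 0.6745.
- 'High specificity' cut-off: 0.6745.
- They coincide at d = 2 × 0.6745 = 1.349, that is AUC = Φ(1.349/√2) = 0.830.

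By symmetry, the specificity at the first cut-off equals the sensitivity at the second; both are Φ(d − 0.6745):

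| AUC | Paired measure | Labels |
|---|---|---|
| 0.70 | 0.527 | hold |
| 0.75 | 0.610 | hold |
| 0.80 | 0.697 | hold, narrowly |
| 0.83 | 0.750 | cut-offs coincide |
| 0.85 | 0.786 | reversed |
| 0.90 | 0.872 | reversed |
| 0.95 | 0.951 | reversed |

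At AUC 0.90, d = 1.812. The 'high sensitivity' cut-off is 1.812 − 0.674 = 1.138 and the 'high specificity' cut-off is 0.674, so the order is wrong. Sensitivity/specificity are 75/87 and 87/75.

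**Step 3: other ROC shapes.** The break-even AUC is 0.810 to 0.830 for a binormal curve with slope b from 0.4 to 2.5 (largest at b = 1), 0.816 for a bilogistic curve and 0.828 for a power-law curve. Without a parametric form:
- A concave curve through the point (false-positive rate 0.25, sensitivity 0.75) has AUC between 0.75 and 1 − 0.125 = 0.875, so reversal is certain only above 0.875.
- For any monotone curve, reversal is certain only above 1 − 0.25 × 0.25 = 0.9375.

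**Step 4: chance in a small validation cohort.** I use a simulation of 33 patients, equal-variance binormal, 10,000 replicates per setting, with assumed PM-positive/negative splits of 5/28, 10/23 and 16/17. It counts how often the 'high sensitivity' cut-off lies above the 'high specificity' cut-off, including replicates in which the two give the same observed sensitivity and specificity.

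| True AUC | Share reversed, range over splits |
|---|---|
| 0.75 | 0.22 to 0.40 |
| 0.85 | 0.59 to 0.74 |
| 0.90 | 0.82 to 0.91 |

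**Step 5: what higher targets do.** With both targets at 90%, z(0.90) = 1.2816. The cut-offs coincide at d = 2.563, AUC = Φ(2.563/√2) = 0.965. The paired measure is Φ(d − 1.2816). At AUC 0.90 this is Φ(1.812 − 1.282) = 0.70. At AUC 0.80 (d = 1.190) it is Φ(1.190 − 1.282) = 0.46.

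**The case against.** The strongest reply is that the consequence is limited. Each label is printed beside its numerical definition, so a careful reader knows what was fixed. The ROC curve, AUC, calibration and decision curve do not depend on these names, and no test or main estimate changes. All of that stands, and it keeps the point modest.

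Three stronger readings are tempting, and the article does not support them:
- *A reader might infer that any model with AUC above 0.83 reverses the labels.* That figure belongs to the equal-variance binormal curve. A concave ROC can stay below 75%/75% with AUC up to 0.875, and in about 33 patients the observed order is partly chance in either direction.
- *A reader might infer that the study aims for an AUC above 0.83.* It states no AUC. The word excellent makes such a value a reasonable reading, but it remains an inference.
- *A reader might infer that neither setting keeps missed cases or false alarms low.* At binormal AUC 0.90 one cut-off misses 13% of cases and the other gives 13% false positives; only the names are wrong. It is true by definition that the 75%-sensitivity cut-off misses one in four cases where it is set. But every patient was CT-negative at entry, and the article sets no minimum that this would breach.

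**Conclusion.** The point holds as a defect in a stated rule. Equal 75% targets without an ordering condition do not guarantee that the cut-offs deserve their names, and the names reverse whenever the ROC curve passes above 75%/75%. That follows from monotonicity alone. The translation into AUC rests on an assumed shape: about 0.83 under the equal-variance binormal model, 0.81 to 0.83 over the parametric shapes tried, and anywhere from 0.75 to 0.875 for a concave curve. The chance figures rest on the minimum sample size and an assumed case mix; a larger cohort would reduce the chance component.

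The rule fails in the situation the authors hope for, a model that predicts well, and it is cheap to repair. It should be corrected, but it does not threaten the AUC or the other accuracy analyses.

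**What to change.** In section 2.10, reconcile the two definitions with their labels:

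1. Require the high-sensitivity cut-off to lie below the high-specificity cut-off, and state in advance what is reported if it does not.
2. Choose targets high enough that the cut-offs are not expected to cross. The value is for the study team; 90% is used above only to show how the crossing point moves.
3. Set both cut-offs on the out-of-fold predictions from the training cohort and apply them unchanged to the validation cohort. This step does not itself prevent crossing. It does ensure that, once the order is right, the labels cannot reverse in validation: the lower cut-off is always at least as sensitive and at most as specific. It also avoids choosing cut-offs on the data used to judge them.

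**Cost.** The text change is small. Higher targets lower the paired measure: at 90% targets and binormal AUC 0.80, the high-specificity cut-off would detect only about 46% of occult PM. Sensitivity and specificity in validation will no longer equal the targets by construction. In addition, out-of-fold scores come from single models while the final score averages several, so some drift from the targets should be expected and reported.
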